### Withdrawal and replacement

Patients can leave the study at any time for any reason. The investigator can decide to withdraw a subject from the study for urgent medical reasons. Patients will not be replaced after withdrawal and will have regular outpatient clinic check-up. These patients will be considered as “lost to follow-up”.

### Sample size

Annually, approximately 450 new women are diagnosed with breast cancer in our surgical outpatient clinic (2011). Approximately 75% of these women are initially treated with BCS. Three operation types are considered: standard, level I and level II. The cosmetic score at 4 weeks is considered the primary outcome variable. From the presently available data the pre-operation level of the cosmetic score appeared to be comparable between the three operation types (*n* = 151; *p* = 0.60). The power calculation will be based on the upper limit of the 95% confidence interval of the pooled within operation type residual standard deviation of the cosmetic score at 4 weeks, adjusted for its pre-operation level. Based on estimates obtained from the present data this residual SD will be set at 16 points on a (0–100)-scale. Two comparisons between operation types will be made: level I with standard and level II with standard. According to Cohen’s *d* a medium effect of 0.5 SD (= 8 points) will be considered to be minimally detectable. The test size alpha of either comparison with the standard operation will be set at a two-sided level of 0.027 according to Dunnett’s *t*, resulting in an overall alpha of 0.05 (two-sided). The resulting sample size per operation type is 75 (80% power) or 100 (90% power). Purpose is to recruit at least 75 patients per operation type, including the patients recruited so far.

### Statistical analysis

Raw data summaries of patient, tumour and treatment characteristics will be made by operation type. Spearman’s correlation and Pearson’s correlation will be used in a descriptive way to assess the correlation of the mean score of total expert panel score, total patient score and automated calculations of the BCCT.Core software. Cosmetic result and quality of life will be measured at *T* = 0, *T* = 1 and *T* = 2. Difference in (changes from baseline of) satisfaction of cosmetic results will be compared between patients undergoing BCS without OPS with those with OPS using linear mixed modelling, with adjustment made for the baseline (*T* = 0) measurement of cosmetic scoring and for other potentially confounding factors such as age, location, size of the tumour and re-operation. The quality of life instruments (EQ5D5L, BREAST-Q, EORTC QLQ C30 and EORTC QLQ BR23) will be analysed similarly after using the prescribed scoring methods when appropriate. The partial correlation of the level of the cosmetic results with the baseline level of each of the quality of life instruments will be analysed after adjustment for operation type. At *T* = 1 and *T* = 2 the partial correlation will be analysed after adjustment for operation type and the baseline level of both the cosmetic result and the quality of life instrument at hand, so as to assess the correlation between changes at *T* = 1 and *T* = 2 from what is known at *T* = 0. Effect of resection volume on the cosmetic score at *T* = 1 and *T* = 2 will be analysed using linear mixed modelling with adjustment for the potentially confounding effects of baseline cosmetic score, age, education, body mass index, tumour quadrant, operation type, possible re-operation and/or complications.

All statistical analysis will be performed with SPSS version 23.0 from IBM Software.

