## Methods

The aim of this prospective cohort study is to assess the additional value of different levels of (oncoplastic) BCS in breast cancer patients with, with regard to quality of life and objective cosmetic outcome, in comparison with conventional lumpectomy combined simple closure of the cavity. Secondly, this study will examine the value of different quality of life scoring systems in evaluating satisfaction with cosmetic results in patients undergoing BCS, with or without the use of oncoplastic techniques.

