#### Cosmetic result

The value of different scoring systems to evaluate satisfaction with the cosmetic outcome in patients undergoing conventional lumpectomy and versus BCS and OPS will be examined [30]. Photographs of the breast will be assessed with quantitative and qualitative scoring systems. Qualitative scoring will be carried out by using a standardized score list for cosmetic result. Both an expert panel and patients will be asked to score the result. Since strong variation between observers is common when measuring cosmetic outcome, the expert panel will consist of at least five members, including both professionals and non-professionals, both male and female with different backgrounds [24]. The panel members will score all photographs individually at all three time points. The pre-operative cosmetic appearance of the breast (*T* = 0) will be used as a baseline and will be scored by a qualitative scoring system by using the adjusted version of the patient self-assessment scoring system, developed by Vos et al. The original 11 items patient self-assessment scoring system of Vos et al., will be used to score cosmetic result at *T* = 1 and *T* = 2 [23].

Haloua et al. have suggested that patient self-evaluation of the cosmetic outcome should be incorporated in future studies apart from other evaluation methods. Self-evaluation reflects the psychological adaptation of the patient to the appearance of the breast [30]. All patients will be asked to score their own photographs at all three time points. Cosmetic appearance of the breast at *T* = 0 and will be used as baseline. A patient version of the scoring list of *Vos* et al. to score the photographs will be used at *T* = 1 and *T* = 2. Evaluation of all scoring systems will be based on the percentage of the total score.

Quantitative scoring will be conducted by using BCCT.Core software that automatically evaluates breast aesthetics. BCCT.Core software is an objective method for the evaluation of cosmetic result in BCS [31]. BCCT.Core software was proven to provide valid cosmetic outcome scores compared to a panel evaluation and is used in several studies [30]. The investigator digitally marks the nipples, axillae and sternum, jugular notch; BCCT.Core software then identifies the relative difference between both breasts and nipples and the relative difference between nipples and inframammary fold difference. (Figure 1: example of BCCT.Core software).

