### Objectives

The aim of this single-centre prospective registration cohort study is to assess the additional value of different levels of oncoplastic BCS in patients with breast, with regard to quality of life and cosmetic outcome by objective measurements of the final cosmetic result in comparison with patients undergoing conventional lumpectomy. Secondly, study trial will examine the value of different quality of life scoring systems in evaluating satisfaction with cosmetic results in patients undergoing BCS.

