## Discussion

The COSMAM Trial is a first prospective cohort study that aims to define the role of different levels of additional OPS in BCS for breast cancer patient. This study compares objective and subjective scoring systems prospectively and is approved by a Dutch medical ethical board.

Since randomization for this type of surgery is virtually impossible the study observes the results of daily practice. This will give a real world experience of current breast saving treatment in an oncological breast cancer centre with multiple surgeons performing different levels of OPS in different patients according to their personal preference. We do realize that in the ideal setting patients with similar tumour types in the same quadrant of the breast should preferably be randomized between lumpectomy with oncoplastic surgery and conventional lumpectomy. However from both an ethical and practical point of view we feel that carrying out such a study could possibly affect cosmetic result and quality of life. Especially in patients with an expected removal of > 10% of the total breast volume as well as large lesions in the upper medial and lower medial and lower lateral quadrants. Based on the reports that application of OPS expands the possibility of BCS thereby still achieving acceptable or good cosmetic results and QoL [19]. Without OPS in these patients a mastectomy would be considered because of high chance of deformation of the breast performing a standard lumpectomy.

All patients who are scheduled for BCS are asked to participate in this study. Our study population is considered to be representative a reflection of the Dutch community.

Despite literature describing the use of OPS there is no clear international standard describing the indications for application of different levels of OPS neither which technique is indicated in relation to the tumour site and the density of the breast tissue. Based on current literature OPS is recommended in patients with a tumour situated in the inner half of the breast, when lumpectomy exceeds > 20% of total breast volume or more than 50–85 ml, regardless of the size of the breast [11–14, 27]. The techniques that are currently used and to what extent they are carried out mainly depends on the surgeon’s preference and expertise.

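### The cosmetic scoring systems are compared by correlation alone, which cannot show whether patients score systematically higher or lower than the panel, or whether that gap differs by operation type (minor)

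*Protocol article*

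**What the plan says.** The Statistical analysis section gives one method for relating the three cosmetic scores to each other. Spearman's and Pearson's coefficients "will be used in a descriptive way to assess the correlation of the mean score of total expert panel score, total patient score"; the last items in that list are "total patient score and automated calculations of the BCCT.Core software". It names no other comparison of these three scores.

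The purpose is described more broadly elsewhere. The Cosmetic result section sets out to examine "The value of different scoring systems to evaluate satisfaction with the cosmetic outcome in patients undergoing conventional lumpectomy" and in oncoplastic patients. The Discussion says: "This study compares objective and subjective scoring systems prospectively".

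The Cosmetic result section also describes the scales. At T=1 and T=2 the panel uses an 11-item list and patients use a patient version of that list. It adds: "Evaluation of all scoring systems will be based on the percentage of the total score". BCCT.Core is a different kind of measure, built on left-right differences derived from marked points on the photograph.

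The formal second aim is a separate matter. The Methods section words it as "Secondly, this study will examine the value of different quality of life scoring systems in evaluating satisfaction with cosmetic results in patients undergoing BCS", and the Objectives section repeats it almost unchanged.

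**The concern.** Comparing scoring systems raises at least two questions: do the scores rank patients alike, and do they give the same value for the same breast? Pearson and Spearman coefficients address only the first. A patient group that rates itself well above the panel, or a panel mean that covers a narrower range, can still correlate strongly with the other score.

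For panel versus patient the second question can be answered, because both use versions of one list on a percentage scale. It has some practical weight. If the patient-panel gap differs between standard, level I and level II surgery, the contrast between operation types depends on who scored, and the planned coefficients would hardly show it. The Sample size section makes the 4-week cosmetic score primary without saying there whose score it is, so readers will want to know how far the scorers differ.

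**Working it through.** **Plan's own figure.** The plan gives no figure for the comparison of scoring systems. Its sample size does reproduce. With d = 8/16 = 0.5 and z = 2.212 for a two-sided alpha of 0.027, n = 2(2.212 + 0.842)²/0.5² = 74.6, or 75 per group at 80% power. For 90% power, n = 2(2.212 + 1.282)²/0.5² = 97.7, or 98, against the stated 100. This has no bearing on the present point.

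**Inputs for the illustration, all assumed.** The SD of both scores is 16. That value is borrowed from the Sample size section, where it is a residual SD adjusted for the pre-operative score and set at an upper confidence limit, so it is not the raw SD of either score. The correlation r and the shift d are chosen values.

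**Formulas.**
- Concordance = 2·r·s₁·s₂ / (s₁² + s₂² + d²)
- Half-width of the 95% limits of agreement, equal SDs = 1.96·√(2·s²·(1 − r))

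**Equal SDs of 16** (2s² = 512):

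| r | d = 0 | d = 8 | d = 16 | Limits of agreement |
|---|---|---|---|---|
| 0.5 | 0.50 | 0.44 | 0.33 | d ± 31.4 |
| 0.7 | 0.70 | 0.62 | 0.47 | d ± 24.3 |
| 0.8 | 0.80 | 0.71 | 0.53 | d ± 19.8 |
| 0.9 | 0.90 | 0.80 | 0.60 | d ± 14.0 |

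Example: at r = 0.8 and d = 8, 2 × 0.8 × 256 / (512 + 64) = 409.6/576 = 0.71, and 1.96 × √(512 × 0.2) = 19.8. Within each row neither correlation coefficient changes.

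**Unequal spread.** With SDs of 16 and 8, r = 0.9 and no shift, 2 × 0.9 × 16 × 8 / (256 + 64) = 230.4/320 = 0.72, while r stays 0.9.

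**Sensitivity to the SD.** With SD 20, r = 0.8 and d = 8, concordance is 640/864 = 0.74 and the limits are d ± 24.8.

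**A gap that differs by operation type.** Take three equal groups with the same panel mean, SD 16 and r = 0.8 within each group. Let patients score 8 points above the panel in one group only. The patient variance becomes 256 + 64 × (1/3)(2/3) = 270.2. The pooled correlation is 204.8/√(256 × 270.2) = 0.78, against 0.80 with no gap. The pooled mean difference is 8/3 = 2.7 points. Yet the contrast of that group with either other group differs by 8 points between the patient and panel scores. Only a mean difference by operation type would reveal this.

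**The case against.** The strongest reply is that the plan does what it says. It offers the coefficients as description of a correlation, and no section names agreement or substitution as a goal. The Cosmetic result section presents self-evaluation as reflecting the patient's psychological adaptation, alongside other methods, which suggests a complement to them. This stands in part: the sentence itself contains no error. But examining the value of the systems and comparing them, as announced, is more than association, and the only stated method stops there.

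It is also fair to say that BCCT.Core measures something different, so correlation is a reasonable tool for both software pairs. That stands, and the remedy is limited accordingly. The two lists are not shown, so their item-by-item equivalence is assumed. A full protocol or analysis plan that is not shown may already include agreement measures.

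Three stronger readings are tempting, and the article does not support them:
- **The second aim goes unanswered.** That aim concerns quality of life instruments. The Statistical analysis section gives it partial correlations with the cosmetic result, adjusted for operation type and, at T=1 and T=2, for both baselines.
- **A high correlation will be taken as interchangeability and enter the decision model.** No section claims interchangeability. The Discussion bases the decision tree on patient and tumour characteristics correlated with a satisfying cosmetic result and quality of life.
- **The error could exceed the 8-point target difference.** A constant gap between scorers cancels when operation types are compared on one score. Limits of agreement describe individual pairs of scores and say nothing direct about a group contrast.

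**Conclusion.** The point holds in a narrow form and is minor. As written, the comparison of cosmetic scoring systems is confined to association. It cannot show whether patients score systematically higher or lower than the panel, and a gap that differs by operation type would barely register in it. The stated second aim and the method of the primary comparison are not affected.

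The actual size is unknown, because the article gives no raw SD, correlation or shift for paired scores. The illustration shows only that a correlation of 0.80 is compatible with concordance anywhere from 0.80 down to 0.53 for shifts of 0 to 16 points, under the assumed common SD of 16. The conclusion about panel versus patient further assumes that the two versions of the list have matching items and scoring direction.

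**What to change.** Keep the Spearman and Pearson coefficients and add to the Statistical analysis section:
- **Panel versus patient, at T=1 and at T=2:** the mean difference with Bland-Altman 95% limits of agreement, and an absolute-agreement ICC, on the percentage scale. Report the mean difference also by operation type. First confirm that the two versions of the list match item by item.
- **BCCT.Core versus panel or patient:** keep correlation. Use weighted kappa only if the scores are put into matching categories.
- **Interpretation:** one sentence saying that no claim of interchangeability with BCCT.Core will be made.

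The cost is a few lines of text and a little more analysis of data already being collected. If a full analysis plan already contains these measures, a reference to it is enough.

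### The Sample size section plans level I and level II each against standard, but the Statistical analysis section compares surgery without OPS with surgery with OPS: two different main comparisons

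*Protocol article*

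**What the plan says.** The aim in the Methods section is "to assess the additional value of different levels of (oncoplastic) BCS in breast cancer patients", with conventional lumpectomy as the comparator. The Objectives section repeats it.

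The Sample size section is built on that aim. It says "Three operation types are considered: standard, level I and level II", and "The cosmetic score at 4 weeks is considered the primary outcome variable". It then says: "Two comparisons between operation types will be made: level I with standard and level II with standard". The alpha for either comparison "will be set at a two-sided level of 0.027" by Dunnett's method, for an overall two-sided 0.05. On the residual spread, "this residual SD will be set at 16 points". The smallest difference of interest is 8 points (0.5 SD). The result is 75 patients per operation type for 80% power or 100 for 90%, and the recruitment goal is at least 75 per type.

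The Statistical analysis section is the only place that describes the between-group model. There, satisfaction with the cosmetic result "will be compared between patients undergoing BCS without OPS with those with OPS using linear mixed modelling", adjusted for baseline and possible confounders. The quality-of-life instruments are to be analysed in the same way. Operation type is named in that section only for the descriptive summaries and as an adjustment term in the partial correlations and the resection-volume model.

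**The concern.** One section has three groups and two contrasts. The other has two groups and one contrast. An analyst who follows the Statistical analysis section literally would code OPS as yes or no, and the result could not say whether level I, level II or both differ from standard. The Discussion and Conclusion want the results to support a decision model on when to use OPS and which technique, so the distinction between levels is what the study is for.

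The Background section gives reason to expect that the levels may behave differently. Level I deals with volume defects below 10% and level II with defects above that, up to 30%. It also cites evidence in both directions on OPS compared with conventional surgery. A combined estimate would depend on how many level I and level II patients happened to be recruited.

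Two candidate main analyses also leave a choice open that should be closed before the outcome data are examined. Data on 151 patients were already in hand when the article's sample size was set.

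**Working it through.** **Inputs.** From the Sample size section: residual SD 16, difference 8, two-sided alpha 0.027 per comparison, 75 or 100 per type. Assumed here: exactly 75 per type, so 150 OPS patients against 75 standard patients; alpha 0.05 for the single two-group test; the same SD of 16; and the true effects by level, which the article does not give.

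**1. The plan's own sample size.** n per type = 2(z_alpha + z_power)² / (8/16)² = 8(z_alpha + z_power)², with z_alpha = 2.2115 for two-sided 0.027.
- 80% power: 8 × (2.2115 + 0.8416)² = 74.6, so 75. Stated: 75.
- 90% power: 8 × (2.2115 + 1.2816)² = 97.6, so 98. Stated: 100.

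The noncentral t gives 76 and 99. The stated figures are reproduced within rounding.

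**2. Power of a level contrast with 75 per group.** SE = 16 × √(1/75 + 1/75) = 2.613, and 8/2.613 = 3.062. Power = Φ(3.062 − 2.2115) = 80.2% (noncentral t: 79.5%).

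**3. Overall alpha.** Two contrasts with a shared control and equal groups are correlated 0.5. With c = 2.2115, overall alpha = 1 − ∫ φ(x)[Φ(x + c√2) − Φ(x − c√2)]² dx = 0.0501. Solving for exactly 0.05 gives 0.02696 per comparison, which rounds to 0.027.

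Steps 1 to 3 show that the sample size, power and alpha are right, and that they belong to the two comparisons of a level with standard.

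**4. Power of the two-group contrast.** SE = 16 × √(1/150 + 1/75) = 2.263. With equal numbers at the two levels, the combined difference is the mean of the two level effects. Power is about Φ(difference/2.263 − 1.96), plus the opposite tail where it matters.

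| Assumed effect, level I / level II | Combined difference | Power, alpha 0.05 |
|---|---|---|
| +8 / +8 | 8 | 94% |
| +4 / +8 | 6 | 75% (noncentral t), 76% (normal) |
| +8 / 0 | 4 | 42% |
| +8 / −4 | 2 | 14% |
| +8 / −8 | 0 | 5% (the test level; no combined difference to find) |

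In every row, a level with a true difference of 8 points has about 80% power in its own contrast at 0.027. A level that differs by 4 points has only about 25% there.

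**5. Sections side by side.**

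| | Sample size | Statistical analysis |
|---|---|---|
| Groups | standard, level I, level II | without OPS, with OPS |
| Contrasts | two, each against standard | one |
| Power with 75 per type | 80% for 8 points at either level | 5% to 94% in the scenarios above |

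**The case against.** The strongest reply is that the level comparisons are already prespecified. The Sample size section says that they will be made, and it fixes the outcome, the time point and the alpha. Nothing says that the Statistical analysis section replaces this. The two-group wording may be loose shorthand, since the same section uses operation type elsewhere, and the Sample size section defines that as three categories. This stands in part: the intent is on record, and the article never says outright that the levels are combined. But two groups is the plain reading of the sentence, it is the only statement of the between-group model, and the quality-of-life analyses take it over.

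A second reply is that combining the levels is not always worse. That is correct. If both levels differ by 8 points, the combined contrast has 94% power, more than either level contrast. The scenarios with unequal or opposite effects are assumptions, and so is the 150 to 75 split, because 75 per type is only a minimum.

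A reader might also infer that the mixed model averages the effect over 4 weeks and 1 year, and so misses the primary time point. The article does not support this. It neither includes nor excludes an operation type by time term, such detail is commonly left to the full protocol or SAP, and the primary time point is stated. Nor is it a fault in itself that the Dunnett level is not repeated in the Statistical analysis section.

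**Conclusion.** The point holds as a contradiction between two sections on the main comparison. A reader might go further and conclude that the study has no planned test of the levels. That is too strong, because the Sample size section plans one; the analysis model does not carry it through.

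If the Statistical analysis section is followed as written, the test cannot attribute a difference to a level, and the stated 80% power and 0.027 do not describe it. The loss or gain in power depends on effects by level that the article does not give. The scenario figures illustrate this for 75 per type, SD 16 and alpha 0.05, and are not predictions. The contradiction itself rests on the text alone and needs none of those assumptions. The sample size calculation is sound.

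**What to change.** In the Statistical analysis section:
- Enter operation type in the mixed model as a three-category factor (standard, level I, level II).
- Name level I minus standard and level II minus standard, on the cosmetic score at 4 weeks, as the primary contrasts with Dunnett adjustment. The level of 0.027 each applies to equal groups. Recruitment is observational with a minimum per type, so recompute it for the achieved group sizes.
- Use the same three-category factor in the quality-of-life models.
- Label OPS versus no OPS as a secondary contrast.

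This costs a few sentences. Sample size and data collection stay as they are. The change should be made before outcomes are compared by operation type.

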#### Diagnostics and treatment characteristics

Baseline characteristics including oncologic data will be collected of all patients containing information about histology, volume of the breast, hormone receptor status, tumour location and tumour size on magnetic resonance imaging (MRI), amount of removed breast tissue during lumpectomy, axillary surgery, re-excision, adjuvant radiotherapy and hormone therapy.

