### Treatment allocation

All patients undergoing breast conserving surgery are requested to participate in this study irrespective of the pre-planned surgical technique to be performed. The decision with regard to the type of surgical technique is not strictly defined but depends on the preference of the individual surgeon taking into account tumour location, breast/tumour ratio, the quality of the breast tissue, breast size and degree of ptosis. In general, surgeons are recommended to perform oncoplastic surgery in case of expected resections of more than 10% of the breast volume as well as large lesions in the upper medial and lower medial and lower lateral quadrants. Planning is done by using shared decision-making. Including informing patients that more extensive procedures may need larger incisions. Surgical procedures are divided as follows:Standard lumpectomy with/without minor volume replacement:Level 1 oncoplastic surgery:Level 2 oncoplastic surgery:

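### Re-operation and complications are adjusted for as confounders although they follow the index operation, so the models do not estimate the total effect of oncoplastic surgery; the size and sign of the shift are unknown

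*Protocol article*

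**What the plan says.** All of the following is in the protocol article.

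- **Operation-type model (Statistical analysis).** A linear mixed model compares cosmetic results with and without OPS. It adjusts for the baseline score and for "other potentially confounding factors such as age, location, size of the tumour and re-operation".
- **Quality-of-life models (same section).** The instruments "will be analysed similarly after using the prescribed scoring methods when appropriate", so the covariates carry over.
- **Resection-volume model (same section).** It is fitted "with adjustment for the potentially confounding effects of baseline cosmetic score" and of "age, education, body mass index, tumour quadrant, operation type, possible re-operation and/or complications".
- **How the operation is chosen (Treatment allocation).** The choice "depends on the preference of the individual surgeon taking into account tumour location, breast/tumour ratio", together with tissue quality, breast size and ptosis. All of these are known before surgery.
- **What is recorded (Diagnostics and treatment characteristics).** The list includes "amount of removed breast tissue during lumpectomy, axillary surgery, re-excision, adjuvant radiotherapy and hormone therapy". Tissue removed at lumpectomy and re-excision are separate items.
- **Primary outcome (Sample size).** "The cosmetic score at 4 weeks is considered the primary outcome variable". The target difference is 8 points and the residual SD is 16, adjusted for the pre-operative score only.
- **Aim (opening of Methods, and Objectives).** To establish what different levels of OPS add over conventional lumpectomy.

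**The concern.** A confounder influences the exposure or shares a cause with it; it cannot result from the exposure. The type of operation is settled on pre-operative features. A re-operation or complication happens afterwards, may depend on the technique or on the volume removed, and may itself worsen the cosmetic result. The plan nevertheless lists these events beside age and tumour size as confounders.

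Two things follow. First, if one technique leads to fewer re-operations, that is part of its value to the patient, and holding re-operation fixed takes that part out of the estimate. If it leads to more, the harm is taken out instead. Second, re-operation can share causes with the cosmetic score beyond the measured covariates. Conditioning on it then links the technique to those causes even if they were balanced before.

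The study is not randomised, so its covariate set carries the causal claim, and the results are meant to feed a clinical decision model. A patient choosing a technique also takes on its re-operation and complication risk.

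**Working it through.** **1. The plan's own figure.** Per-group n = 2(z_α + z_β)² × SD² / δ², with two-sided α = 0.027 (z_α = 2.2115), SD = 16 and δ = 8.

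- 80% power: 2 × (2.2115 + 0.8416)² × 256/64 = 74.6, so 75. The article states 75.
- 90% power: 2 × (2.2115 + 1.2816)² × 256/64 = 97.6, so 98. The article states 100, which agrees to within 2 patients.

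The SD of 16 is adjusted for the pre-operative score only, so dropping re-operation and complications leaves this calculation as it stands.

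**2. Order of events.** Operation type is fixed at or before the index operation; re-operation and complications come later. For resection volume the same order holds if volume means tissue removed at the index lumpectomy, which the separate listing of re-excision suggests.

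**3. Shift through the mediated path.** The article gives neither re-operation rates nor a score penalty, so both are assumptions. With p0 the rate after standard lumpectomy and p1 the rate after OPS:

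adjusted effect − total effect = −(p0 − p1) × penalty

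| Assumed p0 − p1 | Assumed penalty | Shift | Adjusted estimate if the total effect is 8 |
|---|---|---|---|
| 0 | any | 0 | 8.0 |
| +0.07 (OPS lowers re-operation) | 10 | −0.7 | 7.3 |
| +0.15 (OPS lowers re-operation) | 20 | −3.0 | 5.0 |
| −0.07 (OPS raises re-operation) | 10 | +0.7 | 8.7 |
| −0.15 (OPS raises re-operation) | 20 | +3.0 | 11.0 |

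As a share of the 8-point target: 0.7/8 = 9% and 3.0/8 = 38%, in either direction.

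**4. What that means for power.** With 75 per group the standard error is 16 × √(2/75) = 2.613. Power is Φ(effect/2.613 − 2.2115): 80% at 8.0 points, Φ(0.582) = 72% at 7.3, and Φ(−0.298) = 38% at 5.0. This keeps the SD at 16.

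**5. Adding residual tumour extent.** A simulation added an unmeasured factor that raises re-operation and lowers the score by 4 points per SD. It is to be read as what remains after measured size and location. Its assumed correlation with the liability to re-operation was 0.3 to 0.7. Rates of 15% and 8% with a 10-point penalty gave a total shift of 0.9 to 1.1 points. Rates of 20% and 5% with a 20-point penalty gave 3.3 to 3.8 points. Exchanging the rates between the groups reversed the sign. With equal rates (10% each) this simulation showed no shift.

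**6. Timing.** Only a re-operation before the 4-week visit can lie on the path to the primary score. If a later one is entered as a fixed yes/no covariate, the 4-week score is adjusted for a future event. The 1-year score has the longer window and is more exposed. The rate differences in step 3 must therefore be read as rates up to the visit concerned.

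**The case against.** The strongest reply is that nothing in the article shows any bias at all. It gives no rates and no penalty, equal rates produce no shift, and few re-operations may fall before 4 weeks. That stands against any claim about size. It does not rescue the covariate: equal rates cannot be assumed in advance, and in that case the adjustment would remove no confounding either.

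Other points deserve weight:

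- **Tumour extent is partly measured.** Location and size are covariates in the same sentence of the operation-type model. This narrows the second path to residual extent; it does not touch the mediated path. The volume model names quadrant but not size, so it is less protected.
- **The list is illustrative.** The covariates follow a such-as, and a final set may be fixed elsewhere. Re-operation is nonetheless expressly named as a confounder, and the volume model gives its own list, ending in "operation type, possible re-operation and/or complications".
- **Resection volume may be cumulative.** If re-excised tissue counts, re-operation helps determine the exposure and adjusting for it is defensible. The data list points to index volume, but the analysis section does not define it. The volume part of this point is conditional on that.
- **An effect net of re-operation can be a fair question.** It can, but the article does not state that aim or name a direct-effect or mediation analysis.
- **Re-operation may be reported anyway.** Treatment characteristics will be summarised by operation type and re-excision is among them, so part of the remedy is plausibly planned. Complications are not clearly covered.

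**Conclusion.** The plan is wrong as written in calling re-operation, and in the volume model complications, confounders. Adjusting for them answers a different question from the stated aim. This applies to the operation-type and quality-of-life models, and to the volume model if volume is that of the index lumpectomy.

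A reader might infer that the adjustment necessarily removes part of the benefit of OPS, or that 9% to 38% of the 8-point target is lost. The article does not support either. The shift can be zero or of either sign, and 0.7 to 3.0 points rests wholly on the assumed rate differences of 7 to 15 percentage points and penalties of 10 to 20 points. For the same reason the bias cannot be defended as conservative. At 4 weeks it is limited to re-operations that have already happened; at 1 year the exposure is greater. The sample size of 75 or 100 per operation type is unaffected.

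**What to change.** 1. Remove re-operation from the operation-type model and from the quality-of-life models.
2. Remove re-operation and complications from the resection-volume model, and state that the exposure is the volume removed at the index lumpectomy.
3. Adjust for pre-operative variables: baseline score, age, tumour location and tumour size. The volume model also keeps operation type and its other pre-operative covariates.
4. Report re-operation and complications by operation type as outcomes.
5. Keep the currently planned models as labelled sensitivity analyses. In these, count for each visit only events before that visit.

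The cost is wording in the Statistical analysis section and one extra analysis. The sample size does not change.
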